### Randomization

Random allocation of patients with significant SDB (*n* ~ 134) (AHI > 20/h) in a 1:1 ratio to the two treatment arms is performed using a list with permuted blocks and stratified for the study centre and baseline AHI (AHI < or ≥ 45/h assessed by respiratory polygraphy in the screening night, visit 0). The trial statistician generated the randomization list. Study physicians randomize patients using the electronic data capturing system after obtaining the informed consent and evaluating all exclusion and inclusion criteria. No study personnel, except the trial statistician, has access to the randomization list until completion of the trial.

### Intervention: adaptive servo-ventilation

The investigational device for ASV in this trial is the “AirCurve™10 CS PACEWAVE” device, (ResMed Ltd., [name]). It is indicated and approved for clinical use in Switzerland, European Union, and other countries. For this trial, the device is strictly applied in accordance to its approved indications and the instruction manual. Commercially available and approved full-face or nasal masks are used as patient–ventilator–interface to achieve optimal mask fit without relevant leakage. As in clinical routine, all patients will undergo education and training in the use of the device.

In case of an acute upper respiratory tract infection, the intervention will be temporarily or constantly discontinued based on the study physicians and pulmonary physicians’ decision. ASV treatment will be stopped if a patient reports unusual chest pain, severe headache, increased breathlessness or in case of new evidence for congestive heart failure (as defined in the exclusion criteria Table 1) and on patients’ request.

No comparator or sham treatment is administered. SDB patients not randomized to ASV will be treated according to best current medical practice. We decided against sham ventilation due to the following reasons: (1) Sham ventilation may cause even greater distress in patients than effective ventilation and patients will not perceive any benefit in terms of an increase in sleep quality and an improvement in daytime sleepiness. This may lead to a greater decrease in treatment compliance in sham versus effectively treated patients. (2) As described by Tomfohr and colleagues [26], stroke patients’ burden of a ventilation intervention is already high and informing them that they may be randomized to a placebo ventilation will further decrease the number of given informed consents. (3) The use of a subtherapeutic ventilation pressure may act as a partial treatment of nightly occurring apnoeas and hypopnoeas and thus decrease discriminatory power when comparing the two randomized groups.

### Assessment of outcomes

#### Primary outcome: final infarct change from visit 1 to visit 6 on magnetic resonance imaging (MRI)

The infarct volumes (measured in cm^3^) are assessed at visit 1 and visit 6 (see Table 2 displaying which assessments are performed at which visits, according to [27]). We measure infarct volume on DWI (diffusion weighted imaging) MRI scans at visit 1, i.e. after potential lysis therapy and before ASV-treatment, and on T2w MRI scans at visit 6 (see Fig. 2 for illustration). Two independent raters blinded regarding patients’ treatment allocation and presence of SDB assess the primary MRI outcome supervised by two senior neuroradiologists. Change of lesion volume from visit 1 to visit 6 is compared between the treatment groups (SDB ASV+ and SDB ASV−). Change of lesion volume from visit 1 to visit 6 will also be compared between the patient groups with sleep-disordered breathing (SDB ASV+ and ASV− together) and without sleep-disordered breathing (noSDB).

**Table 2 Tab2:**
[figure not shown]
Summary of assessment at each time point according to SPIRIT guidelines

*The following assessments will be collected as long as they are performed within the clinical routine. **Routine analyses: total cholesterol, LDL, HDL, triglycerides, glycated haemoglobin (HbA1c), glucose, C-reactive protein (CRP), thrombocytes, INR, PTT and fibrinogen. Inflammatory markers (optional, depending on funding): MMP-9, TIMP-1, TIMP-4 and sVCAM-1. ***Clinical baseline. Black bars indicate that an assessment can be performed within the indicated timeframe

**Fig. 2 Fig2:**
[figure not shown]
Assessment of primary endpoint. Infarct volume is manually segmented on DWI (diffusion weighted imaging) MRI scans at visit 1, i.e. after potential lysis therapy and before ASV-treatment, and on T2w MRI scans at visit 6. The lesion mask (volume of interest, VOI) is used to preselect the lesion on the T2w images and manual correction is then applied

#### Secondary outcome measurements

##### Demographics

Study physicians and stroke neurologists collect patients’ demographical data during the first 1–2 days following stroke.

##### Stroke data/localization/treatment

At visit 1, study physicians record stroke-specific data such as time of stroke and stroke localization. Antithrombotic treatment before admission (anticoagulation, antiplatelet agents, antihypertensive drugs, cardiac drugs) and thrombolysis at admission is noted. Additional assessments of pre-stroke cardiovascular risk factors are performed: family history, arterial hypertension (BP ≥ 140/90 mmHg measured ≥ 3 times before stroke or patients under treatment for hypertension), diabetes (fasting glucose level ≥ 140 mg/dL or patients treated for diabetes), smoking status, alcohol intake, hypercholesterolemia (cholesterol level ≥ 250 mg/dL or previously under statins) and previous history of coronary heart disease or heart failure, and a validated cerebrovascular risk score (“the Essen Stroke Risk Score, ESRS”) will be determined [28].

##### Medical history including medication

Study physicians record the pre-stroke medical history including medication and treatments at discharge. Assessment of post-stroke medical history including medication is repeated during visit 6 and visit 7 and includes all relevant diseases that (i) have been diagnosed by a physician and/or that (ii) have been treated (pharmacologically or non-pharmacologically).

##### Assessment of stroke severity and clinical outcome

Stroke severity is assessed by means of the NIHSS at admission (visit 0), after 24 h (visit 1), at patient’s hospital dismissal (visit 4) and at the 90 ± 7 days’ follow-up during visit 6.Modified Rankin Scale (mRS) [29] is used to characterize patient’s (in)dependence in daily functioning and in performance of daily activities before the stroke and will be assessed before hospital discharge (between visits 1 and 4).Clinical stroke outcomes are assessed at visit 6 and visit 7 using the Barthel Index (BI) [30] and the mRS [29] as well as patient’s subjective rating about quality of life (EQ-5D-3L) [31].Sensorimotor upper extremity functions are assessed by the Fugl-Meyer Assessment of upper extremities, which has provided to be reliable and sensitive to assess upper-extremity recovery following stroke at 4 to 7 days after stroke and at 3-month follow-up (visit 4 and 6) [32, 33].Death and new cardio-/cerebrovascular events: a composite endpoint of death from any cause, stroke, transient ischaemic attack (TIA), nonfatal myocardial infarction, unplanned hospitalization (or unplanned prolongation of a planned hospitalization) for heart failure or unplanned hospitalization (or unplanned prolongation of a planned hospitalization) leading to urgent revascularization is assessed at visit 4, visit 6, and visit 7 (see Additional file, table 1 for a definition of the events)Cognitive outcomes: Cognitive performance measures, assessed by neuropsychological tests (see Additional file, table 2 for details) of language, neglect, attention, executive functions and verbal and visual short-and long-term memory, are obtained at visit 4 and visit 6.

##### Physiological assessments

Body measurements: Body weight-related measures are assessed at visit 1 and visit 6. Measures include: height in metre and body weight in kg in order to calculate BMI (kg/m^2^), neck circumference, waist (taken at the narrowest waist level) and hip (taken at the level of hip bones) circumference to calculate the Waist/Hip-Ratio (WHR), abdominal circumference (taken at the level of the umbilicus).Blood pressure (BP): (1) acute phase: supine BP is measured at the non-paralyzed arm using a non-invasive BP monitoring device at each site’s stroke unit. Mean systolic and diastolic BP values and minimal and maximum values are calculated for the individual patients. BP variability is calculated by standard deviation, coefficient of variation and maximum minus minimum of both diastolic and systolic values. Night and day parameters can be analysed separately. (2) At hospital dismissal (after visit 4) and at 3 months following stroke (before visit 6): a 3-week BP-monitoring is performed with an ambulatory device (Boso Medicus PC 2, Bosch & Sohn, Germany). Measurements are performed up to 3 times successively, 3 times a day (morning, noon, evening) in a sitting position by the patients themselves or the caregivers. The devices themselves store the measurements automatically. At the same time patients are filling in a diary. Mean systolic and diastolic BP values and minimal and maximum values are calculated for the individual patients over the whole period. BP variability is calculated as mentioned above.Endothelial functioning and arterial stiffness: endothelial function and arterial stiffness is assessed with peripheral arterial tonometry (PAT) (EndoPAT 2000, ItamarMedical Ltd., Caesarea, Israel) in the acute phase at visit 3 and the chronic phase at visit 6 as described in Patvardhan and colleagues [34]. All calculated parameters are summarized in the Additional file, table 3.Blood coagulation parameters and inflammatory blood markers: blood is sampled from a venepuncture for routine and complementary blood tests at visit 2 and 6. Blood sampling for routine analysis of total cholesterol, low- and high-density lipoprotein (LDL and HDL) triglycerides, glycated haemoglobin (HbA1c), glucose, C-reactive protein (CRP), thrombocytes, international normalized ratio (INR), partial thromboplastin time (PTT) and fibrinogen is done according to the hospital protocol and analysed locally. Blood samples of approximately 50 mL are obtained from each patient. Optionally (depending on funding), remaining blood samples will be stored at each site for up to 15 years to be reanalysed for inflammatory markers: MMP-9, TIMP-1, TIMP-4 and sVCAM-1. In the informed consent form, patients are informed and agree with the storage of biological specimens, if applicable.

##### Assessment of ASV treatment compliance

Compliance to ASV treatment is checked daily during the initiation of ASV treatment using the devices internal recordings. Thereafter, verification of compliance takes place at clinical controls at visits 2, 4, 5 and 6. Sufficient compliance is defined as a cumulative ASV use in ≥ 70% of all nights and ≥ 4 h per night in the first 3 months after stroke. All patients who started ASV treatment/training will be analysed as ASV patients (intention to treat; ITT). For secondary analyses, patients with SDB are stratified according to their compliance: compliant patients (per protocol, PP) will be compared to non-compliant participants and to participants who did not receive ASV-treatment.

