#### Second step

Based on the result of the respiratory polygraphy, the lesion diameter confirmed on the MRI at day 1, and after the study physician has checked the remaining exclusion criteria listed in Table 1, eligible patients with significant SDB (AHI > 20/h) are randomized to ASV treatment (SDB ASV+) versus no ventilation treatment (SDB ASV−) applied between the 2nd and 89th night following stroke. Eligible patients with an AHI < 5/h can be included into the control cohort without SDB (noSDB group). Figure 1 gives an overview on the study design.

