### Sleep assessment

Respiratory polygraphy is performed during the first night following stroke onset using a Nox-T3 respiratory polygraph (Nox Medical, Inc., Reykjavik, Iceland), according to standard procedures provided by the manufacturer. This device allows the recording of nasal pressure, snoring, rib cage and abdominal movement, pulse oximetry, activity and body position.

Respiratory polygraphies are analysed by a certified sleep physician immediately on the next day (visit 1, study day 1) to allow inclusion of eligible participants (Fig. 1). Respiratory polygraphies are repeated at visit 6 (day 90 ± 7) to examine the evolution of SDB following a two-week washout period involving a temporary discontinuation of ASV therapy.

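### The ASV compliance rule counts against all nights of the first 3 months, so early death or a permanent protocol-ordered stop is classed as non-compliance, which tilts the secondary compliance contrasts towards compliant patients

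*Protocol article*

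**What the plan says.** The section on assessment of ASV treatment compliance requires "cumulative ASV use in ≥ 70% of all nights", with at least 4 h per night, counted over the first 3 months from the stroke. It equates compliant patients with the per-protocol group and commits, as secondary analyses, to comparing them with non-compliant patients and with patients who received no ASV. It does not say how nights after death, after an ordered stop or during washout are counted.

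Three other places bear on the count:

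- The second screening step has treatment "applied between the 2nd and 89th night following stroke".
- The sleep assessment section places the visit 6 polygraphy "following a two-week washout period involving a temporary discontinuation of ASV therapy".
- The intervention section states that "ASV treatment will be stopped if a patient reports unusual chest pain, severe headache, increased breathlessness", and likewise for new evidence of congestive heart failure and on patient request. For infection the stop may be short: "In case of an acute upper respiratory tract infection, the intervention will be temporarily or constantly discontinued".

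The clinical outcome section defines "a composite endpoint of death from any cause, stroke, transient ischaemic attack (TIA), nonfatal myocardial infarction", together with unplanned hospitalisation for heart failure or for urgent revascularisation, assessed at visits 4, 6 and 7. The statistical analysis section makes the full analysis set the main population. It names ASV compliance as one per-protocol criterion and leaves the full exclusion list to be settled before database closure.

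**The concern.** A compliance measure should describe how a patient used the device while use was expected. Here the denominator keeps running after the patient has died or has been taken off ASV under the protocol. Someone who used ASV every night until then moves to the non-compliant group. A control patient with the same event is kept.

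Death is a component of the composite, and new heart failure is both a reason to stop ASV and closely tied to another component. For these events the outcome helps to decide who counts as compliant. This is separate from fitter patients choosing to use the device more: it would occur even if all patients behaved identically.

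The compliant-group result is likely to be noticed. The discussion expects compliance of about 50% and says that this will affect interpretation. The background cites an earlier CPAP trial with a benefit in compliant users but not by intention to treat. Patients stopped for a suspected adverse effect of ASV are among those who leave the compliant group.

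**Working it through.** The protocol states no cut-off night and no event rate, so there is no figure of its own to reproduce. The sample size calculation is not in question.

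**1. Cut-off night.** Nights 2 to 89 are 88 nights. 0.70 × 88 = 61.6, so 62 nights are needed. With use on every night from night 2, the 62nd is night 63.

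| Denominator | Nights needed | Earliest possible last ASV night |
|---|---|---|
| 88 (nights 2 to 89) | 62 | 63 |
| 90 | 63 | 64 |
| 92 | 65 | 66 |
| 74 (14 washout nights left out) | 52 | 53 |

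These are the earliest nights, for a perfect user. Anyone who misses nights needs to stay on ASV longer.

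**2. Temporary stops.** 88 − 62 = 26 nights may be missed, so a short interruption can leave a patient compliant. If the 14 washout nights lie inside the window and count as missed, only 26 − 14 = 12 remain. The patient must then use 62 of 74 available nights (84%), and an ordered interruption of 13 nights alone causes non-compliance.

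**3. Death by night 89.** Assume the same risk r in both arms, no ASV effect, events spread evenly over nights 2 to 89, and otherwise full use. Let s be the share of events that come too early for compliance. Then

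compliant-group risk = (r − rs)/(1 − rs), and ratio to ASV− = (1 − s)/(1 − rs).

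- Nights 2 to 62 are 61 nights, so s = 61/88 = 0.693. For r = 0.10: 0.307/0.9307 = 0.33. For r = 0.02: 0.307/0.9861 = 0.31.
- With washout nights left out, nights 2 to 52 are 51 nights, so s = 51/88 = 0.580. For r = 0.10: 0.4205/0.9420 = 0.45. For r = 0.02: 0.4205/0.9884 = 0.43.

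**4. Compliant against non-compliant.** The misplaced deaths are also added to the other group. Take 67 ASV patients, half of them willing users (the protocol's expected 50%), and r = 0.10 in both halves. Each half of 33.5 has 3.35 deaths. Of the willing users' deaths, 3.35 × 0.693 = 2.32 are moved.

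- Compliant: (3.35 − 2.32)/(33.5 − 2.32) = 1.03/31.18 = 3.3%.
- Non-compliant: (3.35 + 2.32)/(33.5 + 2.32) = 5.67/35.82 = 15.8%.
- Ratio: about 0.21, with no ASV effect.

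**5. One year.** Assume a 1-year risk of 10% and every event ending ASV. Under a constant hazard, 1.8 points fall before night 63 and the conditional risk afterwards is 8.35%, a ratio of about 0.83. Under a front-loaded hazard (Weibull, shape 0.5), 4.28 points fall early and the later risk is 5.97%, a ratio of about 0.60. If only half of the early events end ASV, the constant-hazard ratio is (0.10 − 0.009)/(1 − 0.009)/0.10 = 0.92.

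**6. Which events end ASV.** Death does. New evidence of heart failure and the listed symptoms order a stop; the article does not say whether ASV may be resumed. Nonfatal stroke, TIA, myocardial infarction and revascularisation are not listed as reasons to stop.

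**The case against.** The strongest reply is that this is a secondary analysis and that its details are still open. The full analysis set, as randomised, carries the main efficacy and safety results, and outcomes are collected after ASV is discontinued, so harms are not lost from the main analysis. The per-protocol list is not final, the article condenses a fuller protocol, and the analysis plan is not shown. The compliance section does not name the composite as an outcome to be split by compliance. Patients who die before visit 6 have no day-90 MRI, so death does not alter the infarct volume contrast among those scanned.

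All of that stands and limits the scope. It does not remove the point: the article itself fixes both the rule and the contrasts, exempts no outcome from them, and gives no other definition of compliance. Permanent ordered stops still move scanned patients between compliance groups.

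A reader might go further and infer that every ordered stop before night 63 means non-compliance, that the compliant group is almost event-free by construction, or that the composite would show a spurious ratio near 0.33. The documents do not support these readings. Infection stops may be temporary and 26 nights can be missed. Several composite components are not reasons to stop ASV. Events after the cut-off, up to 1 year, do not affect compliance.

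It is also fair to object that counting only due nights could label a patient with three nights of use as compliant. The fix should therefore show such patients separately.

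**Conclusion.** The point holds in limited form and should be corrected. On the plain reading of the compliance section, death or a permanent ordered stop before about night 63 makes a patient non-compliant regardless of prior use, with no counterpart in the ASV− group. The cut-off is uncertain (nights 63 to 66, or 53 without the washout nights) because the treatment period and the washout are not reconciled.

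The bias favours compliant patients in both secondary contrasts. It is clearest for death by day 90, with ratios of about 0.31 to 0.45 against ASV− over the assumed 2% to 10% risk and both denominators. Heart-failure events should behave similarly insofar as they lead to a lasting stop. At 1 year, with an assumed 10% risk and every event ending ASV, the ratio is about 0.83 under a constant hazard and 0.60 if events are front-loaded; it is nearer 1 if fewer events end ASV. Event rates and their timing are assumptions, since the article gives none. The full analysis set comparison is not affected.

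**What to change.** Before database closure:

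- In the compliance definition and in the per-protocol compliance criterion, use as denominator only nights on which ASV was due under the protocol. Leave out nights after death, after a permanent ordered stop, during ordered temporary interruptions and during washout.
- Reconcile the stated treatment period (nights 2 to 89) with the two-week washout before the visit 6 polygraphy.
- Report death and permanent ordered stops as categories separate from chosen non-use, and state where stops at patient request belong. Show the per-protocol contrast with and without the death and ordered-stop categories, so that very short exposure is visible.
- For events, compare compliance groups only from a common landmark at the end of the compliance window, among patients event-free at that point in all groups. Do not read earlier events by compliance group causally.

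The cost is a few sentences, plus the date and reason of each stop alongside device recordings that are already collected. The landmark comparison will contain fewer events, and some short-exposure patients must be shown separately. Compliance remains a post-randomisation variable, so the contrasts stay exploratory. No clinical stopping rule changes.

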Effective methods to normalize obstructive SDB are available, including continuous positive airway pressure (CPAP). However, central SDB is also often present in acute stroke. Some studies even suggest that new-onset SDB is often of central type [17, 18]. In particular, central apnoeas and central periodic breathing were also reported in patients with unilateral lesions of variable topography without a disturbed level of consciousness or overt heart failure, which potentially involve autonomic or volitional brain areas participating in respiratory control [19]. Adaptive servo-ventilation (ASV) is considered superior to CPAP in correcting both central and obstructive SDB [20]. Meta-analyses on the initiation of SDB treatment in the very first days following stroke postulate a positive association with neurofunctional improvement with CPAP but with a considerable heterogeneity across the included trials [21]. Prior studies reporting a positive impact of CPAP treatment after acute stroke mainly included TIA patients, milder strokes and younger patients. More recently, Bravata and colleagues found better neurological functioning at about 1 year post stroke, assessed with the modified Rankin scale (mRS) and the National Institute of Health Stroke Scale (NIHSS), in ischaemic stroke patients with obstructive sleep apnoea (OSA) and compliant CPAP use but not in the intention-to-treat analysis [22]. In this study, CPAP was initiated with a median time delay of about 2 months from onset of stroke symptoms. These studies have not assessed the acute neuroradiological evolution or change in network connectivity in the acute stroke phase under ASV treatment versus no treatment.

Thus, eSATIS aims to investigate the effects of immediate treatment of significant SDB (AHI > 20/h) with non-invasive ASV started within 48 to 68 h after stroke onset on the ischaemic lesion evolution assessed by magnetic resonance imaging (MRI) 3 months after the event. The secondary trial objectives assess whether immediate onset of ASV treatment in stroke patients with SDB improves clinical stroke outcomes and physiological parameters. The overall impact of significant SDB compared to no SDB on theses outcomes is also assessed.

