### Statistical analysis

Descriptive summary statistics for efficacy and safety variables will be presented for the entire population and by study arm (no SDB patients, and SDB patients randomized to the ASV+ and ASV- arms). Inferential statistical methods will be used to highlight interesting aspects of the data and primarily for the comparison of outcome variables in the two randomized arms. In addition, comparisons of selected outcomes will be carried out between the two cohorts. The significance level of all statistical tests will be 5% and no control for multiplicity will be applied. Corresponding 95% confidence intervals will be presented as appropriate.

Two main analysis populations will be used:
*Full Analysis Set (FAS)*: this population will include all enrolled patients. In line with the intent-to-treat principle, randomized patients will be analysed according to the treatment group assigned at randomization. The FAS will be the main analysis population for efficacy and safety variables. In particular, it will be the primary population for the comparative analysis of the two randomized treatment groups.*Per-protocol (PP) population*: it will include randomized patients fulfilling all selection criteria and sufficiently compliant with the protocol. The list of criteria, leading to exclusion from the PP analysis, which, among other criteria, will consider the compliance with ASV procedures, will be finalized before database closure for the primary analysis.

The comparative analysis of infarct volume data will be performed using an analysis of covariance model with adjustments at least for the stratification variables used at randomization. In case of violation of the statistical validity conditions for the model, a suitable non-parametric alternative model will be employed, such as the Van Elteren test.

Between-arm comparisons of continuous variables will be performed using the same methodology as for the primary variable, whereas models may include additional explanatory variables, such as the baseline value of specific outcome variables assessed at study end. Logistic regression will be used for comparisons based on binary variables.

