## Discussion

eSATIS trial is the first trial to assess the impact of immediate treatment of significant SDB (AHI > 20/h) in acute ischaemic stroke patients with non-invasive ASV on infarct progression in a prospective interventional randomized controlled design. The trial will give information on the feasibility and efficacy of ASV treatment in patients with stroke and SDB and allow assessing the impact of SDB on stroke outcome. Diagnosing and treating SDB during the acute phase of stroke is not yet current medical practice. Evidence in favour of ASV treatment from a randomized multicentre trial may lead to a change in stroke care and to improved outcomes.

Limitations of this trial include the following: (1) The compliance to ASV is expected to be around 50%. This will have an impact on the interpretation of results. (2) The treatment is open label, which may result in a bias affecting the assessment of secondary clinical outcomes. However, sham ventilation may cause even greater distress in patients than effective ASV treatment without beneficial effects on sleep quality and improvement of daytime sleepiness and is ethically questionable. (3) It is unknown whether the sample size of 134 randomized patients will be sufficient to detect the real treatment effect, since no data on the impact of ASV treatment on the evolution of the lesion volume are available so far.

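### The secondary compliance contrasts and the per-protocol set select on ASV use after randomisation in one arm only; report them descriptively and add a randomisation-based estimate

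*Protocol article*

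**What the plan says.** The section on assessment of ASV treatment compliance sets the rule: "Sufficient compliance is defined as a cumulative ASV use in" at least 70% of nights, with at least 4 h per night, over the first 3 months. It continues: "For secondary analyses, patients with SDB are stratified according to their compliance", and "compliant patients (per protocol, PP) will be compared to non-compliant participants and to participants who did not receive ASV-treatment".

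The Statistical analysis section defines the per-protocol population: "it will include randomized patients fulfilling all selection criteria and sufficiently compliant with the protocol". Its exclusion list, to be finalised before database closure, will consider ASV compliance among other criteria. The same section tests everything at 5% without multiplicity control. For the primary comparison it uses the full analysis set, in which "randomized patients will be analysed according to the treatment group assigned at randomization".

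On expected use, the limitations in the Discussion state: "The compliance to ASV is expected to be around 50" per cent, and add only that this will affect interpretation. The Intervention section lists reasons for stopping ASV, including "severe headache, increased breathlessness or in case of new evidence for congestive heart failure", as well as the patient's own request.

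**The concern.** Whether a patient meets the compliance rule is known only after randomisation, and only in the ASV+ arm. Compliant against non-compliant is an observational comparison within one arm. Compliant against no ASV sets a selected part of one arm against the whole of the other. Neither keeps the balance that randomisation gave. The stopping reasons in the Intervention section show that a worsening clinical course can itself move a patient into the non-compliant group.

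With about half of ASV+ expected to fall short, the intention-to-treat effect is diluted and a null primary result is quite possible. The compliance contrasts could then be read as the answer. The Background describes an earlier CPAP trial with benefit under "compliant CPAP use but not in the intention-to-treat analysis". Selection alone can produce that pattern, although the article gives no evidence that it did so there.

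**Working it through.** **Inputs from the article (Power calculation and sample size; Discussion).** 134 randomised 1:1, so 67 per arm; two-sided 5% t test; SD 20 cm³; d = 0.49; compliance c = 0.5.

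**The plan's own figure.** Noncentral t, 67 per arm, d = 0.49: power 80.4%, which agrees with the stated minimum of 80%. The detectable difference is 0.488 × 20 = 9.75 cm³, in line with the stated figure of about 10 cm³.

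**Dilution.** If the effect is 10 cm³ in compliers and zero in others, the intention-to-treat difference is 0.5 × 10 = 5 cm³. Power is then about 30% (21% at 40% compliance, 41% at 60%).

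**Bias with no ASV effect.** Let b be the amount by which compliers would do better than non-compliers without any treatment effect. This is an assumption; the article gives no value. The control arm contains both types of patient in proportions c and 1 − c, so:

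- compliant v control: bias = b(1 − c) = b/2
- compliant v non-compliant: bias = b

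**Chance of a significant false benefit.** With c = 0.5, about 34 of the 67 ASV+ patients are compliant and 33 are not. This is the upper-tail rejection probability from the noncentral t with SD 20, unadjusted; the nominal value is 2.5%.

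| Contrast | SE (cm³) | b = 5 | b = 10 |
|---|---|---|---|
| Compliant v control (34 v 67) | 20√(1/34 + 1/67) = 4.21 | bias 2.5; 8.5% | bias 5; 21.6% |
| Compliant v non-compliant (34 v 33) | 20√(1/34 + 1/33) = 4.89 | bias 5; 17.1% | bias 10; 52.2% |

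**Check by simulation.** 10,000 trials per scenario, no ASV effect, total SD 20. Two-sided rejection rates were 9.5% and 21% (compliant v control) and 16.6% and 54% (compliant v non-compliant) for b = 5 and 10. The intention-to-treat comparison stayed at about 5%.

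**Randomisation-based alternative, binary version.** Estimate = intention-to-treat difference / 0.5. SE of the intention-to-treat difference: 20√(2/67) = 3.46. SE of the complier effect: about 3.46/0.5 = 6.9. Complier effect detectable with 80% power: 9.75/0.5 = 19.5 cm³ (24.4 at 40% compliance, 16.3 at 60%).

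**Why the 70%/4 h cut-off should not be the main exposure.** Patients below it still receive some ASV. Suppose (assumed) an effect of 10 cm³ in compliers and 5 cm³ in partial users. The intention-to-treat difference is 0.5 × 10 + 0.5 × 5 = 7.5 cm³, and the binary estimate is 7.5/0.5 = 15 cm³, half as large again as the true complier effect.

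**The case against.** The strongest reply is that the plan already contains the problem. The contrasts are labelled secondary, the full analysis set is primary, outcome collection continues after ASV is stopped, and the limitations mention low compliance. Nothing in the article says that the compliance contrasts will carry an efficacy conclusion. All of this stands, and it limits the weight of the point. A reader might infer that the trial's main result is biased; the documents do not support that.

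Second, b is not documented. A reader might infer that mask-tolerant patients are fitter and that a false benefit is therefore likely. The stopping reasons make a link between use and clinical course plausible, but a less impaired patient need not show a more favourable change in lesion volume. With the opposite sign, the bias would hide a benefit. At b = 10 the assumed gap is as large as the trial's whole detectable difference. The exclusion of unstable patients and those unable to follow procedures may narrow it. The cited CPAP trial used functional scales at about 1 year with a late treatment start, so it says nothing about bias in this endpoint. These limits stand, and the percentages are illustrations.

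Third, the analysis plan, which is not shown, may adjust for covariates, and the per-protocol criteria are still open, so 34 against 67 is a projection. That also stands. But the article itself fixes which groups are compared, and adjustment can reduce measured imbalance without restoring randomisation.

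Finally, a complier analysis has assumptions of its own and no more power than intention to treat. A reader might conclude that it should simply replace the planned contrasts, with compliant use as the exposure. The partial-use calculation shows why that goes too far.

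**Conclusion.** The point holds as a matter of interpretation and inexpensive improvement. The planned compliance contrasts and the compliance-based per-protocol set condition on behaviour after randomisation in one arm, and with about 50% compliance they cannot support a causal statement about ASV. Bias arises only if compliers differ in prognosis from the rest. It is then b/2 against controls and b against non-compliers, here 2.5 to 5 and 5 to 10 cm³ for the assumed b. These figures rest on the stated SD of 20 cm³, 50% compliance, no covariate adjustment, and an assumed size and direction of b.

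The primary comparison is unaffected as long as patients are analysed by assigned group, as the Statistical analysis section says.

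**What to change.** 1. State that the compliant v non-compliant, compliant v no-ASV and per-protocol contrasts are descriptive: estimates and intervals, without p-values or causal claims.
2. Add one randomisation-based estimate as the compliance analysis that may support causal statements: two-stage least squares with randomised arm as instrument and device-recorded mean nightly ASV hours as exposure, adjusted for baseline infarct volume and the randomisation strata.
3. Give the binary 70%/4 h version as a sensitivity analysis only, with a note that it overstates the complier effect if partial users also benefit.

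The cost is analysis-plan wording and one model. The devices already record use, and outcomes are collected after ASV is stopped, so no new data are needed. The drawbacks should be stated alongside it: a wide interval (for the binary version, SE about 6.9 cm³ against 3.5 cm³ for intention to treat), no gain in power over intention to treat, and reliance on assignment acting only through ASV use and on a linear effect of hours.
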